## Abstract

**Objective:**

Mindfulness-based cognitive therapy for children (MBCT-C) is an evidence-based intervention that requires further investigation in relation to its effectivness across diverse populations and prolonged follow-up durations. The present study aimed to develop a study protocol to evaluate MBCT-C in addressing internalizing and externalizing problems, as well as attention problems, among children from single-parent families.

**Method:**

A two-arm randomized controlled trial (RCT) using crossover conditions is proposed. The intervention condition will receive twelve weekly sessions of MBCT-C group therapy, while the waitlist (WL) condition will initially serve as a control and then cross over to receive MBCT-C. A total of seventy-six children (aged 10–12) will be randomly allocated to the two study arms. Assessments will be conducted at baseline, post-intervention, and at 3-, 6-, 9-, and 12-month follow-ups. Participants will be assessed by the Kiddie Schedule for Affective Disorders and Schizophrenia-Present and Lifetime Version (K-SADS-PL), and will respond to the Child Behavior Checklist (CBCL), Pediatric Symptom Checklist (PSC), Clinical Global Impressions (CGI), Mindfulness Inventory for Children and Adolescents (MICA), MBCT-C Adherence Scale (MBCT-C-AS), Mindfulness-Based Cognitive Therapy for Child and Parent Evaluation Questionnaire (MBCT-C–CPEQ). Data will be analyzed using a mixed regression model in STATA 18.

**Results:**

As this is a study protocol, no results are available to report at this time.

**Conclusions:**

This study protocol is the first attempt to evaluate the long-term effectiveness of MBCT-C using a crossover RCT that will help develop interventions tailored to internalizing, externalizing, and attention problems among children from single-parent families.

## Introduction

More than two billion children currently live worldwide [1], a number projected to increase by over 60 million in the next two decades [2]. Parent–child interactions [3], parenting practices [4,5], and family structure [6] are recognized as key influences on children’s development and well-being [7]. Political changes, socio-cultural issues, and the loss of one parent have been associated with an increase in single-parent families, which currently account for approximately 6.8% of families worldwide [8]. According to the Statistical Center of Iran, 7.2% of households, or more than one million, 753,960 households, are single-parent households, of which 17% have a male head and 83% have a female head [9]. Evidence shows that parental absence and conflict between separated or divorced parents negatively impact children’s mental and physical health, development, and peer relationships throughout their lives [10].

Disrupted family relationships and the absence of a parent are associated with developmental and mental health challenges in children [11]. One such at-risk group is children from single-parent families, who are at risk of neglect, emotional abuse, and physical abuse due to limited resources and reduced parental capacity [12]. Attention problems and the lack of emotion regulation are also linked to chronic stress in such children. Studies have demonstrated that both internalizing (anxiety and depression) and externalizing (aggression and conduct) problems are prevalent in this population [13].

Considerable evidence supports the effectiveness of cognitive-behavioral interventions in adults [14,15]. However, there are significant challenges associated with applying these interventions to children [16]. In particular, given that these interventions are developed based on metacognition, verbal reasoning, causal and logical thinking, and understanding of emotions, children often struggle to grasp their core concepts [17].

Mindfulness-based cognitive therapy (MBCT) is one of the most promising methods of addressing psychopathology [18]. Earlier studies revealed that mindfulness-based interventions can be used as appropriate psychological interventions to treat mental health problems in children and adolescents [19]. he aim of mindfulness-based interventions is to increase awareness of the present moment and to focus attention on thoughts, emotions, and physical sensations, helping them cope with negative experiences [20]. Thus, these interventions have not only broadened traditional treatments, but have also shown new solutions to address mental disorders.

MBCT for Children [MBCT-C; 21] was developed as a child-specific form of MBCT to provide tailored therapy for children. The protocol was tested across different populations to determine its effectiveness for behavioral issues [18,22–24]. Esmailian, Tahmasian [25] revealed that the MBCT-C have a considerable effectivness on depression, anxiety levels and anger problems among children of divorced parent during 2-month follow-up. Additionally, the increased emotional resilience and mindfulness following this intervention suggest that MBCT-C is a useful intervention for enhancing emotional well-being in children with divorced parents. Findings from another study examining children with cancer found that MBCT-C was highly effective in minimizing internalizing symptoms and attention problems [26]. A study by Wright, Roberts [18] examined the effectiveness of MBCT-C as a preventive intervention for internalizing behavioral problems and found preliminary evidence to support its effectiveness. Findings also suggested that MBCT-C may be a practical and clinically applicable school-based prevention program for reducing internalizing symptoms. Another study of the effectiveness of MBCT on generalized anxiety disorder in elementary school girls found that mindfulness training reduced worry and anxiety [27]. Finally, there is evidence support that MBCT-C can be effective in addressing attention and behavioral disorders as well as anxiety in children [28].

The developmental factors are central to the adaptation of mindfulness-based interventions in children. Semple and Lee [21] that the kind of learning activities that grow out of the tangible sensory experiences allows mindful awareness by enabling children to interact more successfully both with their interior world as well as with the world immediately around them. Since children generally have less developed attentional and memory abilities in comparison to adults, the more developmentally suitable intervention sessions seem to be shorter and repetitive [29]. Furthermore, an adult psychotherapy frequently is based on an abstract thought and verbal emotional understanding, but the emotional experience of children is more shaped in the context of their immediate family and the school. In line with this, parents participation in introductory and review boards, alongside organized communication about home practice has been pointed as an essential element in improving the practice and treatment results in kid-centered mindfulness programs [21].

Based on these developmental concepts, mindfulness-based cognitive therapy with children (MBCT-C) has been precisely developed as a group-based approach to youth between the ages of 9 and 13 years [28], with a view of enhancing social-emotional resilience via development of mindful awareness (Semple et al., 2010). Empirical evidence indicates that there is a significant relationship between attentional problems and behavioral issues in children with high levels of anxiety showing improvements in anxiety and behavioral symptoms after attending MBCT-C [28]. Further research has also supported the effectiness of MBCT-C with anxious child samples. As an example, Shetty, Kongasseri [30] revealed that MBCT-C had been linked to more anxiety and emotion suppression improvements, and emotion regulation. There is also neurobiological evidence that MBCT-C can be associated with more brain activity in interoceptive awareness and internal stimuli processing in anxious youth with a family history of bipolar disorder [31].

Although such encouraging results were obtained, the present evidence base is still remains limited and heterogeneous. Pilot research showed that mindfulness techniques can be effectively implemented in children and potentially reduce symptoms of anxiety, especially the symptoms of attentional functioning at the baseline, however the same studies also revealed the relative lack of rigorous research in pediatric cohorts in comparison to adults [32]. Syeda and Andrews [24] identified significant improvements reported by parents in anxiety symptoms in children receiving MBCT-C, and these improvements were maintained at one-month follow-up, but their research limited generalizability due to the small sample size. Conversely, only significant effects of MBCT-C and cognitive behavioral therapy were found by Wright, Roberts [18] on anxiety, depression and quality of life, but there were no significant differences between mindfulness and sustained attention. These discrepancies provoke significant questions about how exactly MBCT-C has its action and why larger, methodologically sound studies are necessary to make the processes of attention and mindfulness the sources of therapeutic change.

Although the current evidence on the topic of MBCT-C is promising, the available research is still limited in terms of small sample sizes, a comparatively short follow-up, and a lack of randomized controlled trials. Moreover, there is a paucity of research that has specifically investigated the efficacy of MBCT-C in susceptible groups of individuals, including children in single parent families, although there is extensive evidence to suggest that children in single parent families are at a high risk of developing emotional, behavioral, and attentional challenges.

To close these gaps, the current study will involve a Crossover randomized controlled trial (RCT) with a 12-month follow-up to determine the impact of MBCT-C in children from single-parent families. A 12-month follow-up period was selected to allow for the evaluation of both immediate and longer-term effects of MBCT-C across internalizing, externalizing, and attention outcomes. Previous research on mindfulness-based interventions in children and adolescents suggests that extended follow-up periods are necessary to assess the durability of treatment effects and the emergence of delayed benefits [28]. A shorter follow-up duration may not adequately capture the maintenance or decline of treatment gains, whereas longer follow-up periods may increase the risk of attrition and introduce confounding influences related to developmental changes. Therefore, a 12-month timeframe represents a balanced approach to evaluating sustained intervention effects while maintaining methodological feasibility. The hypothesis is that children who receive MBCT-C will show substantial positive changes in central mindfulness dimensions, including self-acceptance, present-moment awareness, and metacognitive awareness. Moreover, participation in MBCT-C is expected to be associated with reductions in internalizing and externalizing problems. Lastly, the intervention is expected to produce meaningful improvements in attentional functioning. Potential gender differences will also be explored to determine whether treatment effects vary between boys and girls.

## Method

### Design

A randomized controlled trial (RCT) with crossover design will be used in this study. The study will involve random assignment of the participants into the mindfulness-based cognitive therapy of children (MBCT-C) intervention group and waitlist control group (WLCG). The participants assigned to the MBCT-C group will undergo a baseline assessment (T1) and will then be subjected to the 12 weekly sessions of the MBCT-C. The outcome measures will be done at the end of the intervention (T2), and after 3-, 6-, 9-, and 12-months (T3-T6). Respondents who are to be part of the WLCG will undergo a baseline assessment at the time of entering the study (T1) and will be kept on the waitlist at the start of the trial. After the MBCT-C group has gone through the intervention period, the participants of WLCG will be given the same 12-session MBCT-C program. The WLCG will undergo post-intervention and follow-up assessment at T3 and 3-, 6-, and 9-month follow-ups respectively (T4-T6). Figs 1 and 2 show the general study design and the evaluation schedule.

**Fig 1 pone.0354802.g001:**
[figure not shown]
Participant timeline: Schedule of enrollment, interventions, and assessments. Note: SPIRIT schedule of enrollment, interventions, and assessments. Abbreviations: K-SADS-PL, Kiddie Schedule for Affective Disorders and Schizophrenia-Present and Lifetime Version; CBCL, Child Behavior Checklist; YSR, Youth Self-Report; CGI, Clinical Global Impressions; MICA, Mindfulness Inventory for Children and Adolescents; MBCT-C-AS, Mindfulness-Based Cognitive Therapy for Children Adherence Scale; MBCT-C-PEQ, Parent Evaluation Questionnaire; MBCT-C-CEQ, Child Evaluation Questionnaire.

**Fig 2 pone.0354802.g002:**
[figure not shown]
Consort diagram of this proposed study protocol.

### Participants

The study will include 76 children aged 10–12 years from single-parent families (either the mother or the father), encompassing both genders in Semnan province, Iran. To be eligible for inclusion, participants must demonstrate borderline or clinical levels of attention problems (T-score ≥ 57) and internalizing difficulties (T-score ≥ 60) on a minimum of two out of four subscales from either the Child Behavior Checklist (CBCL) or Youth Self-Report (YSR) [26]. Exclusion criteria include: (a) significant cognitive impairment or developmental disorder, (b) terminal illness with a prognosis of less than six months, (c) chronic psychiatric disorders (e.g., schizophrenia or bipolar spectrum) or neurodevelopmental disorders per DSM-5, assessed via the Kiddie Schedule for Affective Disorders and Schizophrenia-Present and Lifetime Version [K-SADS-PL; 33], (d) change in parental status to an orphan or a two-parent household, and (e) chronic medical conditions impacting psychosocial functioning. A clinical psychologist will conduct psychiatric evaluations using the K-SADS-PL. Written informed consent will be obtained from parents, and children will provide informed assent.

### Sample size

The sample size for this study will be determined using G*Power software. According to an a priori power analysis, it is assumed that the smallest clinically meaningful difference corresponds to a small effect size (*Cohen’s d* = .20 [34]), with effect sizes smaller than this considered clinically insignificant. Taking into account the three assessment time points (pre-intervention, post-intervention, and follow-up) and the number of dependent variables, a sample size of 38 participants per condition is necessary (*alpha* = .05, *effect size* = .20, *power* = .95). To account for a 20% dropout rate, the total sample size will be 76 children, who will be randomly assigned to either the MBCT-C group (n = 38) or the WLCG group (n = 38).

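### The stated inputs do not give 95% power at Cohen's d = .20 with 38 children per arm, and the total of 76 shows no allowance for the 20% dropout it is said to cover

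*Protocol article*

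**What the plan says.** All of this is in the Sample size section of the protocol article.

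- Software: "The sample size for this study will be determined using G*Power software". The test family is not named.
- Effect: "it is assumed that the smallest clinically meaningful difference corresponds to a small effect size", given as Cohen's d = .20. Anything smaller is described as clinically unimportant.
- Structure: "Taking into account the three assessment time points (pre-intervention, post-intervention, and follow-up) and the number of dependent variables". Neither the within-child correlation nor the number of outcomes is given.
- Result: with alpha .05, effect size .20 and power .95, "a sample size of 38 participants per condition is necessary".
- Dropout: "To account for a 20% dropout rate, the total sample size will be 76 children", "randomly assigned to either the MBCT-C group (n = 38) or the WLCG group (n = 38").

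The Data analyses section plans linear mixed models with the baseline score as a covariate. Under the Design section, the waitlist arm receives MBCT-C once the first arm has finished, so T2 is the only visit that compares treated with untreated children.

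**The concern.** An effect of d = .20 is small, and 38 per arm is far too few to detect it with 95% power in an ordinary two-arm comparison. Repeated measures help, but whether they help enough depends on a test and a correlation that are not stated. The dropout sentence then presents as inflated a total that is exactly twice the number just called necessary.

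The interpretation of the trial is at stake. The section treats effects below d = .20 as unimportant and claims 95% power at that value. A non-significant result would therefore be read as ruling out worthwhile benefit, although the trial would more often than not miss an effect of that size under most of the readings checked here.

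**Working it through.** **Inputs from the article:** d = .20, alpha .05, power .95, 38 per arm (N = 76), three time points, 20% dropout. **Assumed, because not stated:** two-sided test; baseline correlation r; within-child correlation rho.

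**1. Trying to reproduce 38 per arm.** For G*Power's repeated-measures interaction with 2 groups and m = 3 visits, the noncentrality is lambda = N × f² × m/(1 − rho), on m − 1 and (N − 2)(m − 1) degrees of freedom.

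- With .20 entered as f and rho = .5, 95% power needs N = 66. N = 76 gives lambda = 76 × .04 × 3/.5 = 18.24 and power 97.4%.
- N = 76 gives 95% at rho of about .42. It also gives 95% at rho = .5 if alpha is halved to .025.
- N = 60 gives 95.2% at rho = .55, and 60/.8 = 75.

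So several unstated settings lead to about 76. All of them need f = .20, and they disagree on whether dropout is already included.

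**2. Unadjusted two-arm comparison at one visit.** Noncentrality = d × √(n/2) = .20 × √19 = .872 on 74 degrees of freedom.

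- Power is 13.8% two-sided and about 22% one-sided.
- With 30 per arm, two-sided power is about 12%.
- 95% power needs 651 per arm.

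**3. Baseline-adjusted comparison.** The effective effect is d/√(1 − r²). For r = .5 it is .20/√.75 = .231.

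| r | power, 38/arm | power, 30/arm |
|---|---|---|
| .5 | 17% | 14% |
| .7 | 23% | 19% |
| .8 | 30% | 25% |

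95% power with 38 per arm would need r of about .975.

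**4. Three-visit interaction at d = .20, N = 76.** Suppose the arm means are (0, d, d) against (0, 0, 0) in SD units. The differences by visit, centred at 2d/3, are −2d/3, d/3 and d/3. Half of each is the cell interaction effect, so f² = (d²/9 + d²/36 + d²/36)/3 = d²/18 and f = d/√18. Then d = .20 is f = .047, while f = .20 corresponds to d = .20 × √18 = .85. The conversion f = d/2 = .10 belongs to a between-group main effect. It is generous here, since f = .10 corresponds to d = .42 on this pattern.

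| rho | f = .047 | f = .10 |
|---|---|---|
| .3 | 11% | 34% |
| .5 | 13% | 46% |
| .7 | 19% | 68% |
| .8 | 27% | 86% |

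With f = .10, 95% power would need rho of about .86.

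**5. Dropout.** 2 × 38 = 76. After 20% loss, 76 × .8 = 60.8, about 61 children or 30 per arm. Keeping 76 evaluable needs 76/.8 = 95 (96 for equal arms).

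**6. What 76 children can detect.** For 80% power, baseline-adjusted with r = .5 and using the noncentral t, the detectable d is 0.56 with 38 per arm and 0.64 with 30 per arm.

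**The case against.** **The true power is not simply 14%.** A reader might take 14% as the power of the trial. The article does not support a single figure. It describes a three-visit calculation and a baseline-adjusted mixed model, and 14% belongs only to an unadjusted comparison at one visit. Power depends on a test, an effect pattern and a correlation that are not stated. This objection stands, so ranges are given. It does not rescue 95%, which is reached only at r of about .975, or at rho of about .86 with the generous f = .10.

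**The allowance may already be inside the 38.** A reader might conclude that dropout was never added. That is too certain: 30/.8 = 37.5, which rounds to 38, and 30 per arm fits f = .20 with rho = .55. This reading rests on an unstated correlation and goes against the order of the text, which calls 38 necessary before dropout is mentioned. It also leaves the power claim at d = .20 just as wrong. What the text supports is a self-contradiction with no visible allowance.

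**The mix-up of d and f is an inference.** It fits the numbers, but the test family is not named, so it cannot be confirmed.

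**Visits and clustering do not add to the error.** A reader might add that six visits are planned against three in the calculation, or that therapy groups of 8-10 call for a design effect. Extra visits usually add information, and no loss can be shown from them. The article gives no intraclass correlation, and its Data analyses section says the models will adjust for clustering. A condensed article may leave that detail out.

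**Conclusion.** The power claim is wrong as written. At d = .20 with 38 per arm, the readings checked give 14% (unadjusted), 17-30% (baseline-adjusted, r .5-.8), 11-27% (interaction with a persistent effect, rho .3-.8), and at most 34-86% (f = .10, rho .3-.8). None reaches 95%. These figures assume a two-sided alpha of .05, equal arms and no clustering allowance; the correlations are assumptions. A size near 76 needs .20 to be Cohen's f, which on a persistent-effect pattern means d of about .85, more than four times the stated threshold.

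The dropout statement contradicts the sentence before it. If 38 per arm is the requirement, a 20% loss leaves about 61 of the 76 children required. The 30 per arm used above is a worst case at T2, because the article does not say when the 20% is lost, and children who leave later still contribute T2 data.

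**What to change.** Keep 76 children and rewrite the paragraph.

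- Remove the claim of 95% power at d = .20.
- Remove the claim that 76 includes the dropout allowance, or show the number before inflation.
- Name the test, the effect-size metric and the assumed correlation.

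Possible wording:

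> With 38 per arm, and about 30 per arm if the full 20% is lost, a baseline-adjusted between-arm comparison at T2 (r = .5 assumed, no clustering allowance) has 80% power for d of about 0.56 (38 per arm) to 0.64 (30 per arm), and about 14-17% power for d = 0.20. A non-significant result does not exclude d = 0.20.

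This wording takes the T2 contrast as the example. If the sponsor's calculation used another test, the same statement should be made for that test with its own inputs.

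The cost is one paragraph and a less favourable power statement, with no extra children. The Current status section says that outcome data had not been collected at submission, so the change can be made before results exist.

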### Procedure

Registration for this study was completed through the Iranian Registry of Clinical Trials (IRCT20240729062574N1). Recruitment will commence in February 2026 and continue until 76 children are enrolled. Participants will be matched by age and gender and randomly assigned to either the MBCT-C or WLCG group using a computer-generated randomization sequence. The intervention will be conducted in small groups of 8–10 children to maximize group dynamics, and all of the sessions will be conducted by the first author. The data will be collected at the baseline (T1), post-intervention (T2 in the case of MBCT-C, T3 in the case of WLCG), and follow-up (T3-T6 in the case of MBCT-C, T4-T6 in the case of WLCG). Self-report measures (e.g., CBCL, YSR) will be given to the participants by research associates and will be facilitated to make sure that the research participants complete them correctly. At enrollment, semi-structured interviews with the use of the K-SADS-PL will be carried out to verify eligibility. The research design is a single-blind design, whereby the participants do not know certain information about the other group in order to reduce bias. The data will be analyzed by an independent statistician who will be blinded to the group allocations. All the sessions will be audio-taped to make sure that the intervention fidelity is ensured, and recordings will be checked by a clinical psychologist to give feedback to the facilitator. Weekly email notifications will be used to motivate participants to provide data and fill surveys.

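### As the text lists the visits, the waitlist arm is not assessed at T2, so no post-baseline visit compares MBCT-C with no treatment

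*Protocol article*

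**What the plan says.** Two sections of the protocol article set out the assessments by arm, and they agree.

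- **MBCT-C arm (Design).** After baseline at T1: "The outcome measures will be done at the end of the intervention (T2), and after 3-, 6-, 9-, and 12-months (T3-T6".
- **Waitlist arm, before treatment (Design).** These children "will undergo a baseline assessment at the time of entering the study (T1) and will be kept on the waitlist".
- **Waitlist arm, treatment (Design).** "After the MBCT-C group has gone through the intervention period, the participants of WLCG will be given the same 12-session MBCT-C program".
- **Waitlist arm, later visits (Design).** "The WLCG will undergo post-intervention and follow-up assessment at T3 and 3-, 6-, and 9-month follow-ups respectively (T4-T6".
- **Both arms (Procedure).** Data are collected at baseline (T1), then "post-intervention (T2 in the case of MBCT-C, T3 in the case of WLCG", then "follow-up (T3-T6 in the case of MBCT-C, T4-T6 in the case of WLCG".

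The Abstract gives the purpose of the control arm: "the waitlist (WL) condition will initially serve as a control and then cross over to receive MBCT-C". Its list of visits is not split by arm: "Assessments will be conducted at baseline, post-intervention, and at 3-, 6-, 9-, and 12-month follow-ups". Design refers the reader to Figs 1 and 2 for the overall design and schedule; neither figure was available for this review.

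**The concern.** T2 is the end of the first arm's treatment and of the second arm's wait. It is the only time after baseline when one randomised arm has had MBCT-C and the other has not. A waitlist trial gets its efficacy estimate from that visit, and it is the visit the text does not list for the waitlist arm.

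If the trial is run as the two sections read, the waitlist arm cannot do what the Abstract says it is for. Data analyses plans terms for condition, time and period with interaction, but there would be no untreated post-baseline data to distinguish condition from time. The planned comparison of responders between sequences at the end of the intervention would set T2 in one arm against T3 in the other, both after treatment. The waitlist arm would also lack a measurement just before its own treatment, which weakens the within-group comparisons that the Discussion relies on for power. Once the waitlist arm starts its sessions, the missing measurement cannot be recovered.

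**Working it through.** **Step 1. Tabulate the written schedule.** Inputs are the Design and Procedure sentences quoted above. The waitlist arm is treated after the first arm's intervention period, and T3 is its post-intervention visit.

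| Visit | MBCT-C arm | Waitlist arm |
|---|---|---|
| T1 | measured, untreated | measured, untreated |
| T2 | measured, treated | not listed (still untreated) |
| T3 | measured, treated | measured, treated |
| T4 | measured, treated | measured, treated |
| T5 | measured, treated | measured, treated |
| T6 | measured, treated | measured, treated |

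This gives 6 + 5 = 11 observed arm-by-visit cells. After baseline, the number of visits at which both arms are measured and only one is treated is 0.

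**Step 2. Can a treatment effect be estimated separately from time?** Take a fixed-effects model with an intercept, five visit indicators (T2 to T6) and an arm indicator, 1 + 5 + 1 = 7 columns. Add a column for *has already received MBCT-C*. In the 11 observed cells that column is 0 at T1 in both arms and 1 in every later cell, so it equals the sum of the five visit indicators.

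- Written schedule: rank 7 without the treatment column and rank 7 with it. The effect is not estimable.
- Waitlist T2 added (12 cells): rank 7 without the treatment column and rank 8 with it. The effect is estimable.

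Maximum likelihood under missing at random, as planned, does not help, because the waitlist T2 cell is not scheduled for anyone. Forcing a straight line through time would yield a coefficient, but it would rest on the assumed shape of the time trend and not on randomisation.

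**Step 3. What does the T3 comparison estimate?** Let δ be the effect at the end of treatment, δ₃ the effect the first arm still has three months later, and δ_W the waitlist arm's effect at the end of its own course. The expected between-arm difference at T3 is δ₃ − δ_W.

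- Full maintenance and equal response (δ₃ = δ_W = δ): δ − δ = 0, whatever the size of δ.
- Half the gain kept (an illustrative assumption), equal response: 0.5δ − δ = −0.5δ, which favours the waitlist arm although MBCT-C works.
- Delayed benefit (δ₃ greater than δ), equal response: a positive difference that measures later growth of the effect.

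In none of these cases is the difference the effect against no treatment.

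**Step 4. The waitlist arm's own change.** Its T1 to T3 change is the change over the wait plus the change over the 12-session course. With no value at T2 the two parts cannot be separated.

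**Step 5. After the fix.** The T2 contrast would have 38 against 38 children. The standardised difference detectable with 80% power, two-sided 5%, unadjusted, is (1.960 + 0.842) × √(2/38) = 0.64. With 20% dropout (38 × 0.8, about 30 per arm) it is 2.802 × √(2/30) = 0.72. The sample-size justification is a separate matter, and this point does not depend on it.

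**The case against.** The best defence is that the text leaves T2 out but does not rule it out. Procedure labels visits by function: baseline, post-intervention, follow-up. An end-of-waiting visit fits none of these labels. T1 to T6 look like one shared calendar, the Abstract calls the waitlist a control, and a model with condition and period presupposes an untreated period. The schedule figure is where an arm-by-visit grid would normally stand, and it may well show a waitlist T2.

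Much of this stands. A reader might infer that the trial definitely has no control measurement; the documents do not support that while the figures are unseen. Incomplete reporting of an intended visit is at least as plausible. But Procedure says when data are collected in each arm, Design repeats it, and both give T2 to one arm only. The Abstract's list does not fill the gap: it is not split by arm, Procedure defines post-intervention for the waitlist arm as T3, and the list's 12-month follow-up does not exist for that arm, whose follow-up ends at 9 months.

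Two other stronger readings also fail. One is that no randomised question can be answered: early versus delayed treatment remains a valid randomised comparison at T3 to T6. The other is that a test at T3 would be significant only about 5% of the time whatever the true effect. That needs full maintenance of gains for three months and equal response in both arms, and the Introduction treats both decline and delayed benefit as open.

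**Conclusion.** The point holds for the schedule as written in Design and Procedure. On that schedule the waitlist arm has no untreated post-baseline measurement, and the effect of MBCT-C against no treatment is confounded with time. What is lost is the efficacy comparison; the early-versus-delayed comparison survives. The conclusion rests on the text alone. If Figs 1 and 2 include a waitlist T2, the defect becomes a contradiction between text and figures, which still has to be corrected so that sites do not follow the text. In either case it should be settled before the waitlist arm's first session.

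**What to change.** - State in Design and in Procedure that both arms complete all outcome measures at T2 (CBCL, YSR where the child's age allows, PSC, CGI, MICA), and that the waitlist arm does so before its first MBCT-C session.
- Align Figs 1 and 2 with that text.
- Use the T2 between-arm difference as the efficacy contrast against the untreated control. Describe the T3 to T6 between-arm differences as early versus delayed treatment.
- Use T2 as the waitlist arm's pre-treatment value for its within-arm change.

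The cost is one added assessment round for the planned 38 waitlist families and a short amendment, or only a text correction if the visit is already planned. It is feasible: Current status, written as of February 2026, says that no child receives the intervention until recruitment is complete, which is expected in May 2026.
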